### 2.8. Interventions

The interventions will be performed by four Physical Therapists with more than 15 years of experience in the field of neurological PT, who will be blinded to the assessments. Both groups, the EG and the CG, will receive 30 PT sessions for 40 min, 3 times a week, for 10 weeks.

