## Abstract

Background: Stroke survivors experience significant alterations in their daily functionality that has a negative impact on their functionality, participation, and quality of life. Person-centered approaches in Physical Therapy interventions that are focused on functional and meaningful goals help to minimize the impact of the alterations. Therefore, the aim of this study is to assess the effectiveness of a Physical Therapy intervention based on a goal-oriented approach with task-specific training for improving functionality, participation, and quality of life for people with Stroke. Methods: A single-blinded randomized controlled clinical trial will be developed. Adults over 50 years old diagnosed with Stroke over 6 months will be included in this study. Participants (n = 62) will be randomly allocated into two groups: The experimental group (n = 31) will receive 30 sessions, three per week during 10 weeks, of Physical Therapy sessions of goal-directed and task-specific training. The control group (n = 31) will follow the same intervention intensity of their usual Physical Therapy treatment. The primary outcome variables quality of life (NewsQol), participation (Ox-PAQ), and gait functionality (FAC) and the secondary outcome variables functional disability (BI), postural control (PASS), dynamic trunk balance (TIS), and functional goals (GAS) will be measured at baseline, after group interventions (10 weeks), and 6 months after the baseline. Statistical analyses will include repeated-measures ANOVA, Student’s *t*-test, or the Mann–Whitney U-test, with a 95% confidence interval and significance level of *p* < 0.05. Conclusion: Person-centered approaches in Physical Therapy interventions may yield better outcomes in functionality, participation, and quality of life for Stroke patients compared to standardized interventions. Trial registration: ClinicalTrials.gov: NCT06165666 (December 2023).

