#### 2.8.1. Experimental Group Intervention

The EG intervention will be based on functional training with specific tasks related to participants’ daily routine, such as personal hygiene (using the toilet, washing face, brushing teeth, using a towel to dry off), dressing/undressing independently (putting on and changing upper and lower body clothing), preparing food (preparing a pot, turning on the stove, placing prepared food on a plate), basic housecleaning (washing dishes, placing dishes on a rack, using a vacuum cleaner, plugging in and off the houseware), walking and shopping in a store near the home (walking to the store, making a purchase, paying for the product, walking back home), and enjoying simple leisure activities [22,23,24,25].

Each session will begin with the analysis of the characteristics of the task (10 min) to determine the abilities that the person presents and to detect the patterns of movement and components (physical, sensitive, sensorial, social, and environmental) that can be trained in order to improve the performance of the task. The training will be performed progressively, prioritizing the key components of each pattern of movements that will be performed actively by the participants, with successive repetitions (25 min). The last part of the session (15 min) will include the training of the task in different situations and settings.

Therefore, each task, aligned with individual functional goals, will be carried out progressively and systematically. Complex activities will be broken down into simpler tasks, with the difficulty gradually increasing as the sessions progress [23].

The environment/setting is also very important because it can influence the task to be performed and the motor learning process. Therefore, in each session, there will be modifications according to the level of motor learning to facilitate progressive adaptation to different situations, from a controlled environment to a natural environment [46].

The Physical Therapist will consistently work to maintain the individual’s attention and active participation, facilitating the achievement of quality functional movements. This will be achieved by using repetitive activities with variations to promote motor relearning [46].

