#### 2.8.2. Control Group Intervention

Participants assigned to the CG will continue with their standard PT sessions. These sessions will focus on maintaining joint range of motion, practicing transfers from sitting to standing and from standing to sitting, maintaining posture while seated with or without assistance, and performing coordination exercises. Additionally, the CG will engage in activities designed to enhance balance and stability, ensuring a comprehensive approach to preserving and improving functional mobility.

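### Both arms are given 40-minute sessions, but the experimental session's listed parts add up to 50 minutes, so the arms may differ in therapy time by 25% as well as in content

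*Protocol article*

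**What the plan says.** Section 2.8 (Interventions) sets a common schedule: the experimental and the control group alike "will receive 30 PT sessions for 40 min, 3 times a week, for 10 weeks". The Abstract makes the same commitment in general terms: the control group "will follow the same intervention intensity of their usual Physical Therapy treatment".

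Section 2.8.1 (Experimental Group Intervention) sets out the experimental session in three timed parts:

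- Task analysis: "Each session will begin with the analysis of the characteristics of the task (10 min").
- Progressive training of movement components, "performed actively by the participants, with successive repetitions (25 min").
- Practice of the task in varied conditions: "The last part of the session (15 min) will include the training of the task in different situations and settings".

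Section 2.8.2 (Control Group Intervention) gives no component times: "Participants assigned to the CG will continue with their standard PT sessions". The only session length that applies to the control arm is therefore the 40 minutes in Section 2.8.

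**The concern.** Two explicit statements in adjacent sections give different lengths for the same experimental session. A therapist cannot follow both. Keeping to 40 minutes means shortening or dropping part of what Section 2.8.1 describes. Delivering all three parts at their stated lengths overruns Section 2.8 by 10 minutes.

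The trial is meant to test whether goal-oriented, task-specific content does better than usual physical therapy, and equal session number and length is what lets the comparison isolate content. If the experimental arm also receives more time with a therapist, the difference between arms mixes the effect of content with the effect of time. Randomisation does not protect against this, because the difference arises after allocation. None of the analyses in Section 2.9 takes delivered time into account. Two of the primary outcomes listed in Section 2.7, NewsQoL and Ox-PAQ, are questionnaires on quality of life and participation, which extra therapist contact could plausibly influence.

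**Working it through.** **Inputs**

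| Quantity | Value | Source |
|---|---|---|
| Session length, both arms | 40 min | Section 2.8 |
| Frequency and duration | 3 per week for 10 weeks | Section 2.8 |
| Experimental part 1, task analysis | 10 min | Section 2.8.1 |
| Experimental part 2, active repetitions | 25 min | Section 2.8.1 |
| Experimental part 3, varied situations | 15 min | Section 2.8.1 |
| Control session components | no times given | Section 2.8.2 |

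**Step 1: number of sessions.** 3 per week × 10 weeks = 30. This agrees with the stated 30 sessions.

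**Step 2: session length.** Sum of the experimental parts: 10 + 25 + 15 = 50 min. The stated length is 40 min. The figure does not reproduce; the excess is 50 − 40 = 10 min.

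**Step 3: can another reading give 40?**

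- Leaving out the task analysis: 25 + 15 = 40 min. This matches numerically, but Section 2.8.1 says that each session begins with the analysis, which places it inside the session.
- Treating the last 15 min as contained in the 25 min: 10 + 25 = 35 min. This does not match either.

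**Step 4: what each resolution implies for the arms.**

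| Reading | Experimental | Control | Difference over 30 sessions |
|---|---|---|---|
| 40 min governs both arms | 30 × 40 = 1200 min | 30 × 40 = 1200 min | 0, but the listed parts overrun each session by 10 min |
| 50 min applies to both arms | 30 × 50 = 1500 min | 30 × 50 = 1500 min | 0, but Section 2.8 is wrong for both |
| Section 2.8.1 followed for the experimental arm, Section 2.8 for the control arm | 30 × 50 = 1500 min | 30 × 40 = 1200 min | 300 min (5 hours) |

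In the third row the ratio is 1500 / 1200 = 1.25, that is, 25% more time relative to the control arm. Expressed relative to the experimental arm, the same gap is 300 / 1500 = 20%.

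**The case against.** The strongest reply is that the article states equal dose twice, in the Abstract and in Section 2.8, and states unequal dose nowhere. The Section 2.8 sentence covers both groups. If it is right, both arms get 40 minutes; if its figure is a slip, the correction applies to both arms alike. The 25% gap arises only if the figure is wrong for one arm and right for the other. This stands as a limit on the claim: the imbalance is one possible consequence and has not been shown. It does not remove the contradiction. Nor is the third reading far-fetched, since the timed session plan exists only for the experimental arm and Section 2.8.2 contains nothing that would lengthen the control session to match.

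A second reply is that task analysis is assessment, and that the two parts described as training come to exactly 40 minutes. That may explain where the 40 came from. It does not rescue the text, because the analysis is placed within each session. Even on this reading, therapist contact would be 10 minutes longer in the experimental arm unless the control session had a matching part, and none is described. It is fair to add that on this reading the additional 300 minutes would be contact time, not training time.

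A third reply is that extra time would only partly confound the result, and that the article gives no dose–response figure from which to judge how much of an effect 10 minutes could explain. That is correct. The proper statement is that a benefit could not be attributed to content alone.

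Finally, session logs are the kind of detail a journal article may leave to the full protocol. Their absence is therefore not held against the plan, and the finding does not depend on it. A fuller document could settle which figure applies, but it could not make both published statements true.

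**Conclusion.** The concern holds. The components in Section 2.8.1 sum to 50 minutes, Section 2.8 states 40 minutes for both arms, and nothing in the article reconciles them. This part is certain and rests on the article's own figures.

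The size of any imbalance is conditional. It is 10 minutes per session, 300 minutes in all, or 25% of the control arm's total, if the experimental arm follows Section 2.8.1, the control arm follows Section 2.8, and all 30 sessions are delivered at those lengths. It is zero if a single length is applied to both arms. In that case, however, at least one of the two sections misdescribes what is delivered, and the intervention cannot be replicated from the text as it stands.

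The point should be settled before the trial relies on equal intensity to interpret its result. No judgement is made here on which session length is right.

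**What to change.** Reconcile the Abstract, Section 2.8 and Section 2.8.1 so that the experimental component times sum to the stated session length, and so that the length given for each arm respects the equality the protocol already promises. The choice of length belongs to the investigators. If task analysis is meant to fall outside the counted session time, the text should say so and state what the control arm receives in the corresponding period.

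As a useful addition, record delivered minutes per session in both arms and report them by arm, so that equality of dose can be shown. Minutes not recorded during treatment cannot be reliably reconstructed later.

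The cost is small: a correction to the text and, if the addition is adopted, one field on the session log. Sample size, outcomes and the analysis methods are unaffected.

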#### 2.8.1. Experimental Group Intervention

The EG intervention will be based on functional training with specific tasks related to participants’ daily routine, such as personal hygiene (using the toilet, washing face, brushing teeth, using a towel to dry off), dressing/undressing independently (putting on and changing upper and lower body clothing), preparing food (preparing a pot, turning on the stove, placing prepared food on a plate), basic housecleaning (washing dishes, placing dishes on a rack, using a vacuum cleaner, plugging in and off the houseware), walking and shopping in a store near the home (walking to the store, making a purchase, paying for the product, walking back home), and enjoying simple leisure activities [22,23,24,25].

Each session will begin with the analysis of the characteristics of the task (10 min) to determine the abilities that the person presents and to detect the patterns of movement and components (physical, sensitive, sensorial, social, and environmental) that can be trained in order to improve the performance of the task. The training will be performed progressively, prioritizing the key components of each pattern of movements that will be performed actively by the participants, with successive repetitions (25 min). The last part of the session (15 min) will include the training of the task in different situations and settings.

Therefore, each task, aligned with individual functional goals, will be carried out progressively and systematically. Complex activities will be broken down into simpler tasks, with the difficulty gradually increasing as the sessions progress [23].

The environment/setting is also very important because it can influence the task to be performed and the motor learning process. Therefore, in each session, there will be modifications according to the level of motor learning to facilitate progressive adaptation to different situations, from a controlled environment to a natural environment [46].

The Physical Therapist will consistently work to maintain the individual’s attention and active participation, facilitating the achievement of quality functional movements. This will be achieved by using repetitive activities with variations to promote motor relearning [46].

#### 2.8.2. Control Group Intervention

Participants assigned to the CG will continue with their standard PT sessions. These sessions will focus on maintaining joint range of motion, practicing transfers from sitting to standing and from standing to sitting, maintaining posture while seated with or without assistance, and performing coordination exercises. Additionally, the CG will engage in activities designed to enhance balance and stability, ensuring a comprehensive approach to preserving and improving functional mobility.

### 2.9. Statistical Analysis

The Statistical Package for the Social Science software (SPSS^®^ v25) for Mac will be used. An intention-to-treat analysis will be performed. Tests will be carried out with a 95% confidence interval and a statistical significance level of *p* < 0.05. First, descriptive analysis will be performed using means and standard deviations or medians and interquartile ranges otherwise. Normality will be studied through Kolmogorov–Smirnov’s test. For nominal qualitative variables, absolute and relative frequencies will be used. The homogeneity of descriptive and baseline data will be analyzed through Student’s *t*-test for independent samples, Welch’s *t*-test, or the Mann–Whitney U-test. In the case of qualitative variables, Pearson’s χ2 or Fisher’s exact test will be used. Baseline differences will be adjusted through covariate adjustment in regression models. ANCOVA might also be performed to control for baseline differences while comparing the means of the outcome between groups.

To analyze within-group differences between baseline, 6-week, and 6-month assessments, repeated-measures ANOVA or Friedman’s ANOVA will be carried out. To estimate the effect size, partial eta squared will be used. On the other hand, to study the differences between groups, Student’s *t*-test for independent samples, Welch’s *t*-test, or the Mann–Whitney U-test will be carried out. The effect size will be estimated using Cohen’s d or following Grissom’s criteria [47,48,49] in the case of the Mann–Whitney U-test.

Finally, the possible effect of the interaction between descriptive data and independent variables (EG and CG) on the dependent variables will be analyzed through ANCOVA, estimating the effect size using partial eta squared.

Intention-to-treat analysis will be performed in order to reduce, among others, the attrition bias and selection bias that could distort the results. Sensitivity analysis will also be performed in order to address the impact of missing data and ensure the results are as reliable and unbiased as possible.

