### 2.3. Sample Size Calculation

Sample size was calculated using G*Power software 3.1.9.7© (Germany) [30]. In order to detect differences in quality of life in favor of the EG, a large effect size of d = 0.80, an error α = 0.05, and a power of 90% were assumed. Considering a possible loss to follow-up of 10%, the sample size results in 62 participants.

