### 2.5. Randomization and Blinding

Once the inclusion and exclusion criteria are revised, and after every participant signs the informed consent, participants will be included in this study and codified with a number from 0 to 62.

Randomization will be computer-generated by the statistics program Epidat v.4.1 (La Coruña, Spain) with a 1:1 proportion to the experimental group (EG) or control group (CG). This assignment will be blinded to the assessor.

Only the Physical Therapists who will carry out the interventions will have access to randomization.

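### The plan does not settle whether the comparison of arms is adjusted for baseline; one prespecified baseline-adjusted analysis would add precision and remove the open choice

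*Protocol article*

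**What the plan says.** All the relevant text is in section 2.9 of the protocol article.

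- **Comparison of arms.** Differences between groups are studied with Student's t-test for independent samples, Welch's t-test or the Mann–Whitney U-test. The effect size is Cohen's d, or Grissom's criteria with Mann–Whitney. No baseline term is mentioned.
- **Baseline tests.** "The homogeneity of descriptive and baseline data will be analyzed through" the same family of two-sample tests.
- **Adjustment, firm wording.** The next statement on continuous data is: "Baseline differences will be adjusted through covariate adjustment in regression models". No model, covariate or condition is named.
- **Adjustment, optional wording.** Then: "ANCOVA might also be performed to control for baseline differences while comparing the means of the outcome between groups".
- **Repeated measures.** "To analyze within-group differences between baseline, 6-week, and 6-month assessments, repeated-measures ANOVA" or its Friedman counterpart is used, so this analysis concerns change within each arm.
- **Other use of ANCOVA.** ANCOVA is planned firmly only for the interaction of descriptive data with group, which is not the main treatment comparison.

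The abstract lists repeated-measures ANOVA, Student's t-test or Mann–Whitney, and no ANCOVA. Table 2 shows every outcome measured at A0, A1 and A2.

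**The concern.** The hypothesis in the Discussion is that the experimental arm does better than the control arm, so the between-group comparison carries the trial. For that comparison the plan takes three positions: no adjustment, adjustment as a firm intention, and ANCOVA as a possibility. Nothing says which result counts if they differ.

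The firm sentence is about baseline differences and follows directly on the tests of baseline homogeneity. Adjustment therefore seems to depend on what those tests, or the baseline table, happen to show. Under randomisation such tests examine only the play of chance.

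Two things are at stake. The first is precision: the A0 score of each outcome is collected anyway and may explain much of the variation at follow-up. The second is that a model chosen after the data are seen no longer has its nominal properties.

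**Working it through.** **Inputs.** From section 2.3: "a large effect size of d = 0.80, an error α = 0.05, and a power of 90% were assumed", and "Considering a possible loss to follow-up of 10%, the sample size results in 62 participants". From section 2.5: 1:1 allocation, so 31 per arm. The correlation r between the A0 score and the follow-up score is not in the documents. It is assumed and shown from 0.2 to 0.7.

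**1. The plan's own figure.** For an unadjusted two-sample t-test with n per arm, power comes from the noncentral t distribution with 2n − 2 degrees of freedom and noncentrality d × √(n/2).

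- One-sided 0.05: n = 28 gives 90.5%, so 56 in total. 56 × 1.10 = 61.6, rounded up to 62, which is the stated figure. (56/0.90 gives 63.)
- Two-sided 0.05: 34 per arm are needed, so 68 in total, or 75 to 76 after allowing for 10% loss. This does not give 62.

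The sample size thus reproduces as an unadjusted, one-sided t-test. Section 2.3 does not state the sidedness, though its wording is directional: "In order to detect differences in quality of life in favor of the EG". Both readings are carried below with 28 completers per arm.

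**2. Gain from baseline adjustment.** ANCOVA multiplies the residual variance by (1 − r²). The effective standardised effect becomes 0.80/√(1 − r²), with one fewer degree of freedom (53 instead of 54). For r = 0.5: 0.80/√0.75 = 0.924, and the noncentrality is 0.924 × √14 = 3.46, against 0.80 × √14 = 2.99 unadjusted.

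| r (assumed) | Variance factor 1 − r² | Effective d | Power, two-sided | Power, one-sided |
|---|---|---|---|---|
| Unadjusted | 1 | 0.80 | 83.6% | 90.5% |
| 0.2 | 0.96 | 0.816 | 85.1% | 91.5% |
| 0.3 | 0.91 | 0.839 | 86.9% | 92.7% |
| 0.5 | 0.75 | 0.924 | 92.4% | 96.1% |
| 0.6 | 0.64 | 1.000 | 95.7% | 98.0% |
| 0.7 | 0.51 | 1.120 | 98.4% | 99.4% |

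The formula ignores chance imbalance in the covariate. Simulation (100,000 trials at 28 per arm) gives slightly lower two-sided ANCOVA power: 86.2%, 91.9% and 98.3% at r = 0.3, 0.5 and 0.7.

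**3. What an open choice does.** The same simulation, two-sided 0.05:

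- t-test or ANCOVA, each fixed in advance: type I error about 5.0%.
- ANCOVA only if the baseline test has p < 0.05, otherwise the t-test: type I error 4.9%, 4.3% and 3.6% at r = 0.3, 0.5 and 0.7. Power is 83.8%, 84.6% and 85.5%, so most of the ANCOVA gain is lost.
- The smaller p-value of t-test and ANCOVA: type I error 6.5%, 7.3% and 8.3% at the same r.

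The last two are illustrations. The protocol states neither rule, but its wording excludes neither.

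**4. Change scores.** Section 2.9 does not say whether the t-test compares follow-up or change scores. A change-score t-test has simulated two-sided power of 69.9%, 83.7% and 96.7% at r = 0.3, 0.5 and 0.7, below ANCOVA each time.

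**The case against.** The strongest reply is that the plan does intend adjustment, in firm words, and that a t-test fixed in advance is a valid analysis of a randomised trial. Both statements are right. A reader might infer that the baseline data go unused; the sentence on covariate adjustment rules that out. What remains is that the sentence names no model or covariate and stands beside an optional ANCOVA and unadjusted tests.

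Other stronger readings also go beyond the text:

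- **A p-value decides on adjustment.** The homogeneity tests and the adjustment sentence are adjacent, but no such rule is written. It is a plausible reading only.
- **Baseline imbalance biases the result.** At 31 per arm the largest non-significant gap is 2.000 × √(2/31) = 0.508 SD, and at r = 0.6 about 0.30 SD of it would carry into follow-up scores. That is the boundary case. The median absolute chance gap is about 0.17 SD, carrying about 0.10 SD, and the t-test's standard error already allows for such chance gaps.
- **Efficacy will be read from change within one arm.** The section separates within-group from between-group analyses and gives each its own test and effect size. The lack of a stated group-by-time term in a condensed article is not a fault in itself.
- **Power falls short because baseline is omitted.** The step from 90.5% to 83.6% comes from one-sided against two-sided testing, which is a separate matter.

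It could also be said that such detail belongs in a statistical analysis plan. That does not answer the point: the protocol names the between-group tests and makes ANCOVA optional, so a later plan with ANCOVA as primary would have to override it.

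**Conclusion.** The point holds as an unreconciled and improvable choice of analysis, not as an invalid one. Section 2.9 leaves the primary comparison open between unadjusted and adjusted analysis and appears to tie adjustment to observed baseline differences.

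The cost is mainly precision. With 28 completers per arm and d = 0.80, prespecified ANCOVA adds between about 1.5 points (r = 0.2) and 15 points (r = 0.7) of two-sided power, or about 1 to 9 points one-sided. The gain rests wholly on r and is negligible near r = 0. It is computed against a comparison of follow-up scores. The second cost, dependence of the result on choices made after seeing data, cannot be sized from the documents, because no selection rule is stated.

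The change should be made, since it uses data already planned, but the trial is not unsound without it.

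**What to change.** Rewrite the between-group paragraph of section 2.9 before any outcome data are examined:

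- **NewsQoL, Ox-PAQ and Barthel Index.** Name one primary between-group analysis, used regardless of any baseline test: ANCOVA of the follow-up score on arm and the same score at A0, reporting the adjusted mean difference with its 95% CI at A1 and at A2. A mixed model with baseline, arm, visit and arm-by-visit is an alternative that also handles missing visits. The two are not equivalent once visits are missing, and 10% loss is expected, so choose one.
- **FAC.** Use a baseline-adjusted ordinal model, since linear ANCOVA suits a 0 to 5 category scale poorly. The abstract lists the FAC as primary and section 2.7 lists it as secondary, so state the model either way.
- **Baseline tests.** State that baseline p-values do not decide whether or how to adjust, or drop them.
- **Within-arm ANOVA.** Label it descriptive.
- **t, Welch and Mann–Whitney tests.** Keep them as sensitivity analyses.
- **Abstract.** Bring its list of methods into line.

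The cost is wording only: every outcome is already measured at A0, and no further data or participants are needed.

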### 2.7. Outcome Variables

Outcome variables will be collected at 3 points: at baseline (A0), at the end of the group interventions (A1), and 6 months after baseline (A2). The assessments will be carried out by 2 Physical Therapists, members of the research team, after training and consensus meetings. The assignment will be blinded to the two physical therapist assessors. Sociodemographic variables (Table 1) are age, sex, duration of Stroke, work status, type of Stroke, affected hemibody and comorbidities.

*Primary variables* (Table 2) are as follows:-Quality of Life: Measured with the Spanish version of Newcastle Stroke-Specific Quality of Life Measure (NewsQoL), developed by Buck et al. [32] to measure the quality of life of people after a Stroke. It consists of 56 items distributed in 11 dimensions. The range of scores varies from 0 to 3 points for each of the items. In each dimension, a result is obtained from 0% to 100%, with a higher score representing a worse perception of quality of life. It is adapted and validated in the Spanish population [33] and it has proven to be sensitive and reliable [34].-Participation: Measured with the Oxford Participation and Activities Questionnaire (Ox-PAQ), an instrument for measuring participation and activity levels based on the International Classification of Functioning, Disability and Health (ICF) [35]. It consists of 23 items divided into 3 dimensions: routine activities, social commitment, and emotional well-being. Each item is scored on a Likert scale from 0 to 4 points. Higher results mean greater difficulty in participation [35]. It is valid for people who have suffered a Stroke [36], and the Spanish version is up to be done.-Functionality: Measured with the modified Barthel Index [37], used to assess the functionality of activities of daily living of people with neuromuscular and/or musculoskeletal pathology, especially in those who have suffered Stroke. The total score ranges from 0 to 100, where 0 indicates complete dependence and 100 indicates complete independence. It is cross-culturally adapted and validated in the Spanish population [38].

**Table 2 jpm-14-00891-t002:** Outcome variables.

Outcome Variables	Assessment Period			Measuring Instruments
	Baseline	Post-Treatment	Six Months after Baseline	
Perception of Quality of Life	x	x	x	NewsQoL-S.V.
Participation in the environment	x	x	x	Ox-PAQ
Functional disability	x	x	x	BI
Gait functionality	x	x	x	FAC-S.V.
Postural control	x	x	x	PASS-S.V.

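### Arm-by-descriptor interaction tests are planned without restriction or multiplicity control at p < 0.05, and power for them is low

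*Protocol article*

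**What the plan says.** The Statistical Analysis section (2.9) sets one rule for all testing: "Tests will be carried out with a 95% confidence interval and a statistical significance level of *p* < 0.05". After the within-group and between-group comparisons it adds a last analysis: "the possible effect of the interaction between descriptive data and independent variables (EG and CG) on the dependent variables will be analyzed through ANCOVA", with size expressed by "estimating the effect size using partial eta squared". The verb is a commitment; elsewhere in the same section an optional ANCOVA is worded as something that might be done.

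The sets to which this sentence refers are listed elsewhere:

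- **Descriptors.** Section 2.7 gives them as "Sociodemographic variables (Table 1) are age, sex, duration of Stroke, work status, type of Stroke, affected hemibody and comorbidities". That is seven items. Table 1 has eight rows because work status is split into status before the stroke and current status.
- **Outcomes.** The abstract names three primary outcomes, "The primary outcome variables quality of life (NewsQol), participation (Ox-PAQ), and gait functionality (FAC"), and four secondary ones, "the secondary outcome variables functional disability (BI), postural control (PASS), dynamic trunk balance (TIS), and functional goals (GAS"). Section 2.7 instead places the Barthel Index among the primary variables and FAC among the secondary ones, but the total is seven either way, as in Table 2.
- **Visits.** "Outcome variables will be collected at 3 points", two of them after baseline (A1 and A2).

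**The concern.** A blanket plan to test effect modification at an uncorrected 0.05 level produces significant results by chance in proportion to the number of tests. The trial was sized for one main effect on quality of life, so it has little ability to find real modifiers among them. At stake is the reporting of who benefits: an apparent modifier such as affected side, stroke type or work status could be read as guidance for tailoring treatment. The Discussion invites that reading, since it hopes the findings will inform personalised intervention protocols. The comparison between arms is not affected.

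**Working it through.** **1. The plan's own figure.** Section 2.3 gives d = 0.80, α = 0.05, power 90%, 10% loss and 62 participants. A two-sample t-test with one-sided α = 0.05 needs 28 per arm, 56 in all, and 56 × 1.10 = 61.6, rounded up to 62. (Two-sided α would need 34 per arm, 68 in all, before any allowance for loss.) So 62 is reproduced, with 56 evaluable, for the quality-of-life main effect only. The article gives no figure for interactions.

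**2. Number of tests.** Full reading: 8 × 7 = 56 per visit and 56 × 2 = 112 over two visits. With the seven descriptors of the text: 7 × 7 = 49 and 98. NewsQoL counts here as one outcome; analysing its 11 dimensions separately would raise the count.

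**3. Expected false positives if no interaction exists.** 56 × 0.05 = 2.8 and 112 × 0.05 = 5.6. With seven descriptors, 49 × 0.05 = 2.45 and 98 × 0.05 = 4.9. These expectations do not depend on correlation between tests.

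**4. Chance of at least one false positive.** Under independence this is 1 − 0.95^k: 0.943 for k = 56 and 0.997 for k = 112. The outcomes share patients, so independence is an upper case. A null simulation with 62 participants (1,500 runs per setting; each model has arm, one descriptor and their product) gave:

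| Assumed correlation between outcomes | 56 tests | 112 tests |
|---|---|---|
| 0.3 | 0.91 | 0.99 |
| 0.5 | 0.88 | 0.97 |
| 0.7 | 0.77 | 0.92 |

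These correlations, the correlations between visits (0.7 to 0.8) and the descriptor frequencies are assumptions; the article gives none.

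Narrower readings:

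- Three primary outcomes at both visits (48 tests): 0.82 by simulation.
- NewsQoL at both visits (16 tests): 0.50 by simulation.
- NewsQoL at one visit (8 tests): 1 − 0.95^8 = 0.34.

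**5. Does the sample size drive this rate?** Repeating the simulation with 300 participants gave 0.92, 0.87 and 0.78 for 56 tests, and 0.98, 0.96 and 0.92 for 112. The rate is practically unchanged.

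**6. Power for an interaction.** For a binary modifier with share p and 28 evaluable per arm, in SD units, SE = √(2/(28p) + 2/(28(1 − p))), with 52 degrees of freedom and a two-sided 0.05 test (critical t = 2.007).

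- p = 0.50: SE = 0.535. For an interaction of 0.80 SD the noncentrality is 0.80/0.535 = 1.50, and power is 31%.
- p = 0.15: SE = 0.748, noncentrality 1.07, power 18%.
- For comparison, the 0.80 SD main effect with 28 per arm has 84% power two-sided (91% one-sided).
- With p = 0.50, power is 11% for an interaction of 0.40 SD and 84% for one of 1.6 SD.

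**7. Exaggeration.** With p = 0.50, an estimate must exceed about 2.007 × 0.535 = 1.07 SD to reach significance. A true interaction of 0.80 SD could therefore be declared only with an estimate at least 1.07/0.80 = 1.34 times too large, taking the SD at its true value.

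**The case against.** The strongest reply is that the sentence never says that each descriptor is tested on each outcome at each visit. The 56 and 112 are the natural reading of open wording, not a stated count, and on narrower readings the chance of a false positive falls to between 0.34 and 0.82. A journal article is also condensed, and a full protocol or analysis plan that is not shown may restrict the set or label it exploratory. That part stands as a limit on the size of the problem. It does not remove it: the published text makes a commitment and attaches a threshold to it, and even the narrowest reading considered has about seven times the nominal error rate (0.34/0.05 = 6.8).

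Three stronger conclusions that a reader might draw are not supported:

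- **Spurious modifiers are practically certain.** This fits 112 tests, but not 56 strongly correlated tests (0.77) or tests confined to the primary outcomes.
- **The small sample causes the false positives.** It does not, since the rate is the same with 300 participants. The sample size causes the low power.
- **No realistic interaction can be detected.** Power of 31% or 18% is low, not nil, and the article gives no basis for what size is realistic.

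The analysis also comes last in its section, and the study hypothesis concerns only the contrast between arms. Misuse of a chance finding is therefore a risk in reporting and not something the plan promises.

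**Conclusion.** The point holds as a minor one about the analysis plan. As written, Section 2.9 fixes an open set of interaction tests at an uncorrected 0.05. On the full reading, 2.8 to 5.6 false positives are expected under a global null, and the chance of at least one is about 0.77 to 0.94 for 56 tests and 0.92 to above 0.99 for 112. Low power is a separate defect: about 31% (even split) or 18% (15/85 split) for an interaction of 0.80 SD with 56 evaluable. Together they mean that a significant interaction would be disproportionately likely to be false or too large. The figures rest on the full reading of the wording, the global null, the assumed correlations and frequencies, and a binary modifier for the power calculation. The primary comparison stands regardless.

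**What to change.** Replace the interaction sentence in Section 2.9 with one that does the following:

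- names a small set of modifiers, chosen in advance from data already collected (for example time since stroke);
- examines them on quality of life, the outcome on which the sample size is based, at one stated post-baseline visit. The visit has to be named because the article designates no primary time point, and the outcome because it lists three primary variables;
- reports each interaction as an estimate with a 95% CI, labelled exploratory and with no significance claim;
- labels any other interaction analysis exploratory in the same way.

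The cost is a change of wording and somewhat less analysis. No new data are needed. The small downside is fewer subgroup results to report.
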